### Sample size

The only available study on patient satisfaction, our primary outcome, between IRA and IPAA reports 98% and 88% satisfaction for the methods respectively [15]. However, they only asked the IRA patients that still had their IRA in place after a mean of 11 years making it a little difficult to interpret. Another study compared QALYs between IRA and IPAA and reports a mean of 33.42 for IRA and a mean of 31.57 for IPAA [13]. With an estimated 3 SD (it was 2.8 for IRA and 4.5 for IPAA) and the significance level 0.05 and 80% power that difference would require 43 patients in each group to demonstrate a difference. Due to the mentioned shortcomings of the study comparing satisfaction we regard the latter study more relevant and decided to aim at a minimum of 50 patients in each group. Deliberately a little over the power estimation to avoid any effect of possible loss to follow-up.

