### Statistical analysis

Analysis will be conducted according to the intention-to-treat principal. The primary outcome satisfaction, a proportion, will be compared with chi-square test. For the primary outcome two-tailed tests will be applied since the null hypothesis is that there is no difference between the two reconstructive methods. Secondary outcomes assumed to be normally distributed will be compared between the two study arms using t-tests. Functional and QoL variables will be analyzed with mixed model ANOVA analysis. Time to failure will be analyzed with multivariate cox-regression analysis. Kaplan–Meier curves will be constructed and compared with log-rank tests. Repeating events, such as reoperations, will be analyzed with multivariate Poisson-regression.

There is no data and safety monitoring committee since all treatment is according to established practice. We do not plan to perform any interim analysis.

From a statistical point of view our choice of primary endpoint is not optimal because we have no reason to expect any difference between the two study arms. Still, to our opinion, this is the most important outcome measure.

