Considering late complications, pouchitis for IPAA is reported in between 36–48% of cases [31-33] with increasing cumulative numbers over time and up to 70% at 20 years follow up [33]. Some degree of proctitis at some point is reported in between 59–76% of IRA cases [34, 30]. There is to our knowledge only one report that specifies reoperation rates after IPAA and none on IRA. In the only available publication Wasmuth et al*.,* reports a reoperation rate of 33% after a mean follow-up of 10 years and estimates that 52% of IPAA patients will have had at least one reoperation after 20 years [35].

Regarding bowel function, the main issues are continence, number of bowel movements, need to evacuate the bowel during nighttime and urgency to evacuate the bowel. For IRA, between three and six bowel movements per 24 h have been reported [30, 36-39] while for IPAA between five and seven bowel movements are reported [30, 40]. Need for night-time evacuation have been reported in 13–41% of IRA patients and 53% of IPAA patients. Among IRA patients, faecal incontinence is reported in 5% of patients and seepage or need for protective pads for 11–19% of patients [36, 39]. For the IPAA patient these figures are 14% and 32–39% [39, 41] Urgency is reported in 33–68% of IRA patients compared with 16–23% of IPAA patients [36, 39, 42, 43].

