## Trial status

As of September 28, 2022, we have enrolled 37 IRA patients and 11 IPAA patients in the study arms and 23 IPAA and 18 ileostomy patients in the control arms.

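### Poisson regression is named for repeated reoperations with no allowance for overdispersion; if model-based standard errors are used and reoperations cluster, type I error exceeds 5% by an amount the protocol does not determine

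*Protocol article*

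**What the plan says.** The Statistical analysis section of the protocol article gives one sentence to recurrent events: "Repeating events, such as reoperations, will be analyzed with multivariate Poisson-regression". Nothing is said about the variance estimator, dispersion, an offset for follow-up or dependence between events in one patient. The same paragraph does plan a mixed model for the functional and QoL variables.

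Reoperations are listed among the data to be collected. The nearest declared endpoint is complications, which is secondary. Sidedness is fixed for the primary outcome only ("For the primary outcome two-tailed tests will be applied").

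The Discussion offers one set of background figures, for IPAA alone. The cited study "reports a reoperation rate of 33% after a mean follow-up of 10 years" and estimates that 52% will have had at least one reoperation by 20 years. The protocol says that it knows of no such figures for IRA.

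On numbers, the investigators "decided to aim at a minimum of 50 patients in each group". At the September 2022 status, "we have enrolled 37 IRA patients and 11 IPAA patients in the study arms".

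**The concern.** The sentence itself calls the events repeating. Model-based Poisson standard errors are right when the variance of the counts equals their mean, given the covariates, so that one reoperation says nothing about the next. In reconstructive surgery a complicated or failing reconstruction tends to bring several operations to the same patient. If so, the variance exceeds the mean, the standard error is too small by the square root of the ratio, and differences between arms are declared too readily.

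Because the protocol knows of no published reoperation rate after IRA, this trial's rate ratio may be used in patient counselling. An interval that claims too much precision would mislead there.

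**Working it through.** **The plan's own figures.** There is no stated error rate, event count or dispersion for this analysis to reproduce. The only design figure is 43 per group for a difference of 33.42 − 31.57 = 1.85 with SD 3 at "the significance level 0.05 and 80% power". The normal formula gives 2 × (1.960 + 0.842)² × 3² / 1.85² = 41.3, so 42. The t-based version gives 42.26, so 43. It reproduces, and the present point does not depend on it.

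**Step 1: large-sample error.** Let φ be the variance-to-mean ratio. A model-based z statistic is too large by √φ, so the true two-sided error is 2 × [1 − Φ(1.96/√φ)]. Two-sided testing is assumed here.

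| φ (assumed) | 1.96/√φ | true error |
|---|---|---|
| 1.0 | 1.96 | 5.0% |
| 1.1 | 1.87 | 6.2% |
| 1.25 | 1.75 | 8.0% |
| 1.5 | 1.60 | 11.0% |
| 2 | 1.39 | 16.6% |
| 3 | 1.13 | 25.8% |

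Doubling the error needs φ = 1.42; tripling it needs φ = 1.85.

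**Step 2: what the Discussion figures suggest about φ.** Read the 33% as patients with at least one reoperation, treat everyone as followed for 10 years, and assume a constant rate for each patient.
- With no variation between patients, the 20-year figure would be 1 − 0.67² = 55%, close to the quoted 52%.
- With gamma-distributed rates, P(no event) = (1 + aμ)^(−1/a), where μ is the mean count and a the heterogeneity. Put x = aμ at 10 years. Both figures are matched when ln(1 + 2x)/ln(1 + x) = ln 0.48/ln 0.67 = 1.83, so x = 0.222. Check: a = ln 1.222/(−ln 0.67) = 0.50, and 1.222^(−2) = 0.67, 1.444^(−2) = 0.48.
- Hence φ = 1 + x = 1.22 at 10 years and 1 + x/2 = 1.11 at the trial's five years.

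The fit is fragile. With 50% at 20 years, the same equation gives φ = 1.22 at five years; with 54% it gives 1.03.

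**Step 3: finite samples.** Gamma-Poisson counts were simulated with equal means in both arms, no covariates and 40,000 trials per setting. The share with any reoperation by five years was set to 1 − √0.67 = 18%. Trials with an event-free arm count as non-rejections for the Wald test.

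| φ | 50:50 Wald | 50:50 LR | 37:11 Wald | 37:11 LR |
|---|---|---|---|---|
| 1.00 | 4.1% | 5.3% | 2.7% | 7.5% |
| 1.11 | 5.3% | 6.8% | 3.3% | 8.8% |
| 1.22 | 6.4% | 8.0% | 3.8% | 10.0% |
| 1.49 | 9.7% | 11.2% | 5.4% | 12.9% |
| 1.82 | 13.6% | 15.2% | 7.3% | 16.6% |

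At 37:11 the likelihood-ratio (LR) test is already off at φ = 1, so part of its excess there comes from few events and not from clustering.

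**Step 4: a mechanism in the protocol.** A failed IRA may be converted to an IPAA, usually with a loop ileostomy, and the patient stays in the IRA arm under intention to treat. Five-year IRA failure is given as 10–16%. Assume other reoperations are Poisson with mean m, every failure brings one operation, and a share q brings a second (loop closure counted as a reoperation).
- m = 0.1, q = 1, failure 10%: mean 0.1 + 0.2 = 0.30; variance 0.1 + 4 × 0.1 × 0.9 = 0.46; φ = 1.53.
- m = 0.3, q = 0.5, failure 10%: mean 0.3 + 0.15 = 0.45; variance 0.3 + (0.25 − 0.0225) = 0.5275; φ = 1.17.

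Moderate clustering is therefore plausible, but it rests on assumed counts.

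**The case against.** The strongest reply is that the named model is not itself what inflates the error; an unstated model-based standard error would. A Poisson regression with robust or dispersion-scaled variance fits the sentence, and a full protocol or SAP, not shown here, may specify one. This stands to the extent that nobody can say from the article that naive standard errors will be used. It does not remove the point: the article commits to a method for events it calls repeating, and that method at its default lacks the needed allowance.

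A reader might infer that false positives will be two to three times too frequent. The documents do not support that. It needs φ of about 1.4 to 1.9, and no figure in the article supplies it; the only rough anchor, from IPAA data alone, gives about 1.1. That anchor cannot exclude stronger clustering either.

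A reader might also infer that the inflation is the same at the 37:11 split. It is for the likelihood-ratio test, but the Wald test stays at about 3–7% over the ratios simulated.

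Finally, the planned model is multivariable, and covariates may absorb some of the variation between patients. The simulations have none.

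**Conclusion.** The point holds in a limited form. Poisson regression is named for recurrent events without provision for overdispersion. If reoperations cluster and model-based standard errors are used, intervals are too narrow by a factor √φ, and the type I error exceeds 5% by an amount that the protocol does not fix. With 50 per group it is about 5–7% if φ is near 1.1 and about 10–11% if φ is near 1.5. These ratios are assumptions. The lower one rests on a constant-rate reading of a single IPAA report, and there is no corresponding IRA figure.

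The outcome is secondary, and neither the chi-square test of satisfaction nor the sample size is affected. Severity is minor.

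**What to change.** Replace the sentence with negative binomial regression, or Poisson regression with an estimated dispersion, with log follow-up time as offset. Name the test and the interval method.

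Add that inference stays approximate under any of these choices while one arm is small. In the simulations robust standard errors gave 4.6–6.2% at 50:50 for φ of 1.11–1.82, but 2.9–3.3% at 37:11. Dispersion-scaled tests, in a separate set of simulations with means of 0.3–0.8 reoperations per patient, gave 5–6% at 50:50 and 5.5–9% at 37:11. The negative binomial model was not simulated.

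The cost is one sentence of text, a different model call and somewhat wider intervals. If clustering proves absent, little is lost.

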## Discussion

Reconstruction after colectomy is a morbidity-associated as well as a resource-intensive activity with the sole purpose of enhancing function, QoL and patient satisfaction. The actual disease has already been treated with the colectomy. Hence it is crucial to provide patients and care givers with the best possible information on the risks and benefits of each reconstructive treatment. They should be informed of what to expect if they choose to keep their end ileostomy permanently. There are no prospective head-to-head comparisons between IRA and IPAA in UC patients published.

The aspects to consider when evaluating a reconstruction after colectomy are early as well as late complications of the reconstruction, bowel function as well as urogenital and sexual function, quality of life (QoL), patient satisfaction as well as risk of failure and/or rectal cancer. There are also patient preferences which must be considered.

The IRA is easier to perform and does not require pelvic dissection, but instead the preserved rectum demands continuous topical medication and the risk for rectal cancer remains [25-27]. Hence, patients with an IRA needs to be surveilled for cancer and patients with increased colorectal cancer risk (i.e. patients with previous colorectal cancer or primary sclerosing cholangitis (PSC) are not considered suitable for IRA [25].

Early complications generally refers to complications within 30 days of surgery and they are most often graded according to the Clavien-Dindo scale [22]. In most studies a Clavien-Dindo score of 3b (a complication requiring intervention under general anesthesia) is considered to be of clinical significance. For IPAA, Clavien-Dindo scores of 3b or worse are reported in between 10–18% of patients [28, 29]. The only available report on early complications after IRA reports a 12.4% incidence of Clavien-Dindo 3a (a complication requiring intervention under local/regional anesthesia) or worse [30].

Considering late complications, pouchitis for IPAA is reported in between 36–48% of cases [31-33] with increasing cumulative numbers over time and up to 70% at 20 years follow up [33]. Some degree of proctitis at some point is reported in between 59–76% of IRA cases [34, 30]. There is to our knowledge only one report that specifies reoperation rates after IPAA and none on IRA. In the only available publication Wasmuth et al*.,* reports a reoperation rate of 33% after a mean follow-up of 10 years and estimates that 52% of IPAA patients will have had at least one reoperation after 20 years [35].

Regarding bowel function, the main issues are continence, number of bowel movements, need to evacuate the bowel during nighttime and urgency to evacuate the bowel. For IRA, between three and six bowel movements per 24 h have been reported [30, 36-39] while for IPAA between five and seven bowel movements are reported [30, 40]. Need for night-time evacuation have been reported in 13–41% of IRA patients and 53% of IPAA patients. Among IRA patients, faecal incontinence is reported in 5% of patients and seepage or need for protective pads for 11–19% of patients [36, 39]. For the IPAA patient these figures are 14% and 32–39% [39, 41] Urgency is reported in 33–68% of IRA patients compared with 16–23% of IPAA patients [36, 39, 42, 43].

The pelvic dissection associated with IPAA constitutes a risk for impaired sexual function and impaired fecundity. Sexual function is described and compared in different ways in IPAA studies and the results are difficult to compare [44-49]. In female patients with an IPAA, sexual dysfunctions is reported in up to 50% of cases [44, 45] using validated sexual function forms, e.g. the FSFI [20, 21, 50, 51]. Fewer problems are reported among male IPAA patients and there are even reports of improved sexual function after surgery [52, 53]. There is, to our knowledge, very little published on the impact of IRA on sexual function [25]. However, Moreira et al*.,* reported a tendency towards better sexual function among IRA patients compared to IPAA patients [39]. The actual reproductive rate is referred to as fecundity. Female UC patients are reported not to have impaired fertility compared to the general population [54]. Fecundity in female UC patients dropped from normal levels to 0.2 after IPAA [55] and infertility rates have been reported to increase from 20 to 63% after IPAA in a meta-analysis consisting of studies with both UC and FAP patients [56]. There is a reasonable hope that laparoscopic surgery may reduce the functional problems after IPAA but that remains to be further investigated [57, 58]. It was previously suggested that IRA does not reduce fecundity/fertility [59, 60] In contrast, Challine and colleagues recently compared fecundity between females subjected to IRA and IPAA and found no significant difference between the two [61]. This was in turn contradicted by the findings from the Swedish national cohort published by Druvefors [62]. In the French cohort they found reduced fecundity among females subjected to open surgery compared to laparoscopic regardless of IPAA or IRA [61] while the number of laparoscopic procedures was to few to render further analysis in the Swedish material [62].

In reconstructive surgery, the goal is to improve quality of life (QoL). Still, it is not obvious how to assess and compare QoL in surgery for UC [63]. In studies comparing IPAA to end ileostomy, an improved body image was reported among the IPAA patients but otherwise similar satisfaction and QoL [64-67]. There are several studies investigating how QoL develops over time in IPAA patients. It appears that the QoL of the IPAA patients is somewhat impaired in the first months after surgery but then improves [68, 69] and the QoL of the IPAA patients appears to be good in the long-term [42, 70]. Available studies comparing QoL in IRA to IPAA reports similar [15, 71] QoL between the two procedures but one study reported more urgency affecting work and dietary restrictions among the IRA patients [72].

Failure, defined as excisions or permanent deviation, is reported in between 4–9% of IPAA cases at 5 years and 7–19% at 10 years [30, 73-78] and reports with longer follow up indicates a continuing annual failure rate of around 2% even after 15 years [79]. The reported failure rates for IRA are 10–16% at 5 years and 24–31% at 10 years [30, 34, 39, 80, 81]. One should remember that after excising a poorly functioning IRA it is possible to construct an IPAA. However, the options after excising an IPAA are either a redo IPAA or an end ileostomy [82].

The obvious limitation with our study design is the lack of randomization. As mentioned in the introduction we have made an attempt to randomize between IRA and IPAA but after receiving detailed information, patients decline randomization and insist on choosing a reconstructive method themselves, with similar numbers opting for IRA and IPAA. We do not consider it a risk, but a fact, that some degree of selection bias will occur as some patients are more concerned regarding pelvic surgery, and its possible consequences, while others are more concerned by the need of anti-inflammatory medication, endoscopic surveillance and the risk of rectal cancer. We aim to minimize such effects with the provision of standardized information whenever possible. Because this is a multicenter study the same consultant cannot present the oral information to every patient. Instead, all patients will be shown the same information video by the consultant IBD Surgeon.

We do, however, see an upside to the lack of randomization. It is of interest to see what patients choose when presented with standardized information and if there are any demographic patterns in the choice of reconstructive method. Furthermore, we do not think that IRA will necessarily be a better choice than IPAA but rather it will be equally good in the selected cohorts eligible for either restorative procedure. Patient involvement may also increase the chance of a favorable outcome.

Another question that we hope to address is if there are any differences in the outcome of IPAA between the patients that were eligible for both IRA and IPAA and the patients that had IPAA as their only restorative option, i.e. will the level of proctitis affect the outcome of IPAA.

The multinational setting of the study will also allow for detection of possible differences in the attitude towards functional outcomes and complication patterns between the Swedish and English UC population. It will also improve the external validity of our study.

## Conclusion

Because we have failed to enroll patients in an RCT we believe this is the best available way to compare the outcomes between IRA and IPAA. This design will also provide a good overview of the entire UC population that required colectomy.

## Trial status

As of September 28, 2022, we have enrolled 37 IRA patients and 11 IPAA patients in the study arms and 23 IPAA and 18 ileostomy patients in the control arms.

## Data Availability

Not applicable, no data, only protocol.

## Abbreviations

IBD: Inflammatory bowel disease
UC: Ulcerative Colitis
CD: Crohn’s disease
IBD-U: Inflammatory Bowel Disease-Unclassified
QoL: Quality of Life
CI: Continent ileostomy
IPAA: Ileal pouch anal anastomosis
IRA: Ileorectal anastomosis
PSC: Primary Sclerosing Cholangitis
RCT: Randomized controlled trial
SF-36: Short form 36 item
SHS: Short health scale
FSFI: Female Sexual Function Index
IIEF: International Index of Erectile Dysfunction
TaTME: Trans anal total mesorectal excision
